##### Caregivers

There is no medical CRF for caregivers, but a brief CRF on background data, co-morbidities, and use of healthcare services.

##### Statistics

The design makes it possible to evaluate the effect of an early integration of oncology and PC at the institutional and patient levels across intervention and control arms, by comparing the use of chemotherapy in the last 3 months of life.

Analyses on the primary outcome will be performed when there are 300 patients in each arm with data on chemotherapy use in the last 3 months of life, which is the basis for the power estimation. Standard descriptive statistics will be used for background variables. Further, data will be analyzed by the intention-to-treat approach; mixed effect regression models will be used to analyze both primary and secondary endpoints in order to account for clustering. Logistic and linear regression models will be used respectively for binary and continuous outcomes and all models will be adjusted for potentially relevant baseline covariates at patient level, i.e. sex, age, diagnosis, performance status score, and baseline symptom scores. The analysis of the main outcome will also be adjusted by size of the catchment areas, which is the randomization stratification factor.

Survival analysis methods, i.e. Kaplan–Meier curves and Cox proportional hazards models with shared frailty terms to account for clustering and Kaplan–Meier curves, will be employed in order to model time to death. Sensitivity analyses to different methods will be applied to handle missing data in the secondary PROs: complete case analysis and multiple imputations. This also applies to patient- and caregiver-reported outcomes. Paper forms will be used to collect medical data and PROs for comparisons across arms.

Further, a potential effect of the intervention at each of the centers in the intervention arm may be evaluated at a later stage as an explorative outcome by comparing post-intervention data with historical data, e.g. on use of chemotherapy and number of readmissions/emergency admissions in the very last stages of life as appropriate.

The CONSORT recommendations for reporting RCTs will be followed. The CONSORT recommendations for reporting C-RCTs will be followed. IBM SPSS Statistics for Windows, version 25.0 (IBM Corp., Armonk, NY, USA) and STATA (Stata Corp. LCC, College Station, TX, USA) will be used.

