### Sample size

Sample size calculation was based on the primary endpoint: the proportion of patients who receive chemotherapy during their last 3 months of life (Table 1). This took into consideration the predetermined number of 12 as the total number of clusters, i.e. hospitals, that was chosen for contingency/feasibility reasons and allowing for intra-cluster correlation coefficient (ICC) in the range of 0.06–0.09, which is usually considered appropriate for process outcomes. In addition, calculations were performed to provide 80% power at the two-sided 5% level to detect a 25% difference in chemotherapy use between the two arms, i.e. 20% versus 45% in the treatment and control groups, respectively [61]. The choice of the clinically relevant treatment effect used for sample size calculation (25% difference for chemotherapy administration) was based on both clinical judgment and previous data [62, 63]. Effects on power increase due to adjustment by baseline measurements and other covariates (see statistical analysis section for the full list of covariates proposed) were also considered, allowing for correlation coefficient between outcome and adjustment covariates (r_adj_) up to 0.4. Table 2 reports sample size per treatment arm for various values of ICC and (r_adj_).

**Table 2 Tab2:** Sample size per treatment arm for various values of ICC and (r_adj_)

			**r**_**adj**_		
	*0.4*	*0.3*	*0.2*	*0.1*	*NO*^a^

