**ICC**					
*0.06*	102	120	138	150	150
*0.07*	126	150	180	198	204
*0.08*	156	204	258	**300**^b^	312
*0.09*	210	318	468	630	714

*ICC* intra-cluster correlation coefficient, *r*_*adj*_ correlation coefficient between outcome and adjustment covariates

^a^No adjustment for baseline covariates

^b^Required no. of patients per arm

A sample size of 300 patients in each arm, with a total of 600 patients, was chosen as it accounts for an ICC up to 0.08 even with a low r_adj_ (no less than 0.1) and for an ICC up to almost 0.09 in case of r_adj_ no less than 0.3. Due to an expected attrition rate up to 12%, 340 patients per arm (680 in total) will be enrolled.

The 12 hospitals were grouped into three strata according to size of catchment area, to decrease the chance of imbalance in cluster characteristics between trial arms. Each cluster consisted of four hospitals: small (69,000–136,000 inhabitants); medium (169,000–282,000 inhabitants); and large (300,000–492,000 inhabitants) (Table 3). This procedure is considered a reliable and easy to measure proxy for other cluster characteristics, potentially impacting on the study outcome. Effect of the variability in cluster size (mean 50, SD 19.5, CV [Coefficient of variation] = 0.39) was calculated through the approach proposed by Van Breuckelen [64]. For CV = 0.39, this method indicates low inflation factors which are in the range of 2.8%–2.2%, for ICC in the range of 0.06–0.09, respectively [64]. The role of the correlation coefficient in sample size formula for binary outcomes and when adjusting for baseline factors is explained by Hemming et al [65]. Sample size calculations in Table 2 were undertaken using the module clustersampsi [65] implemented in the statistical package Stata (Stata Statistical Software, Release 14, Stata Corp., College Station, TX, USA).

**Table 3 Tab3:** Presentation of stratification, randomization results, and sample size at cluster level

Intervention arm				Control arm			
Hospital	Stratification	Inhabitants	Patients	Name	Stratification	Inhabitants	Patients
Stavanger University Hospital, Stavanger	1	352,650	85	Akershus University Hospital, Nordbyhagen	1	490,000	85
Oslo University Hospital	1	340,000	85	St. Olavs Hospital/Trondheim University Hospital, Trondheim	1	300,000	85
Østfold Hospital Trust, Grålum	2	282,600	50	Sørlandet Hospital, Kristiansand	2	170,000	50
Vestfold Hospital Trust, Tønsberg	2	233,000	50	Telemark Hospital Trust, Skien	2	169,000	50

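### With 12 hospitals in three strata, the planned mixed logistic regression holds its 5% level only with a small-cluster correction; uncorrected, it rejects about 8–15% of null trials

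*Protocol article*

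**What the plan says.** The Sample size section takes "the predetermined number of 12 as the total number of clusters", six per arm, and reports that "calculations were performed to provide 80% power at the two-sided 5% level to detect a 25% difference in chemotherapy use between the two arms", the rates being "20% versus 45% in the treatment and control groups, respectively". It works by "allowing for intra-cluster correlation coefficient (ICC) in the range of 0.06–0.09". It then explains that "The 12 hospitals were grouped into three strata according to size of catchment area", four hospitals to a stratum, with randomization inside each stratum.

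For analysis, the Statistics section states that "mixed effect regression models will be used to analyze both primary and secondary endpoints in order to account for clustering": logistic for binary outcomes and linear for continuous ones, with patient-level covariates. For the primary outcome only, it adds: "The analysis of the main outcome will also be adjusted by size of the catchment areas, which is the randomization stratification factor". SPSS and Stata are named as software. The article does not give the estimation method, the test statistic, the reference distribution or the degrees of freedom.

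**The concern.** Hospitals were randomized, so the information about the arm effect is limited by the number of hospitals, however many patients each one contributes. With an intercept, an arm term and two stratum terms, 12 − 1 − 1 − 2 = 8 between-hospital degrees of freedom remain. Two things then go wrong in an uncorrected mixed model. Maximum likelihood underestimates the between-hospital variance because it ignores the four fixed effects estimated from 12 hospitals. A normal or chi-square reference then treats that variance as known.

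The design calculation did allow for few clusters (shown below), but the analysis text does not carry that through. If the model is run uncorrected, the primary confidence interval is too narrow and the stated 5% level does not hold for a trial intended to change national practice.

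**Working it through.** **Inputs.** Rates 0.20 and 0.45, two-sided 5%, 80% power, k = 6 hospitals per arm, ICC 0.06–0.09, covariate correlation r from 0 to 0.4, and 300 analysed per arm (Sample size section and Table 2). Planned hospital sizes are 85/85/50/50/35/35 per arm (Table 3).

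**Step 1: reproduce Table 2.** The formulas are:
- n = (c + z₀.₈₀)² × [0.20×0.80 + 0.45×0.55] / 0.25², multiplied by (1 − r²)
- patients per hospital m = n(1 − ICC) / (6 − n×ICC), rounded up
- patients per arm = 6m

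For the chosen cell (ICC 0.08, r = 0.1):
- With c = t(0.975, 10 df) = 2.228: n = (2.228 + 0.842)² × 0.4075/0.0625 = 61.44; × 0.99 = 60.83; m = 55.96/1.134 = 49.35, so 50. Result: **300, as stated**.
- With c = 1.96: n = 51.17; × 0.99 = 50.66; m = 46.61/1.947 = 23.94, so 24. Result: 144.

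Over the whole table, t on 10 df gives 18 of 20 cells exactly. The other two differ by one patient per hospital (318 against 312, and 636 against 630). Normal quantiles give none of the 20, with pooled or unpooled variance.

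**Step 2: closed-form check of the level.** For equal hospitals and a normal outcome, maximum likelihood divides the between-hospital sum of squares by 12 instead of 8, so the Wald statistic is too large by √(12/8).
- ML with z, strata in the model: P(|t₈| > 1.96 × √(8/12)) = P(|t₈| > 1.600) = 14.8%
- REML with z, strata in the model: P(|t₈| > 1.96) = 8.6%
- ML with z, no strata: P(|t₁₀| > 1.96 × √(10/12)) = 10.4%

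**Step 3: simulation under no effect.** 12 hospitals, Table 3 sizes scaled to 300 per arm, random-intercept logistic model with arm and strata, fitted by maximum likelihood; 2,500 trials per setting, Monte Carlo SE about 0.7 points. The settings combine ICC 0.06–0.09, event rates 20–45%, two shapes for the hospital distribution, and 300 or 340 per arm. The REML-type rows come from a linear mixed model on the hospital proportions (5,000 trials at each of ICC 0.06, 0.08 and 0.09).

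| Inference, strata in model | Rejection at nominal 5% |
|---|---|
| ML, Wald z | 13.4–14.9% |
| ML, likelihood ratio | 11.0–12.6% |
| ML, Wald against t(8) | 8.7–9.3% |
| REML-type, z | 8.4–8.9% |
| REML-type, t(8) | 5.0–5.7% |
| Hospital-level regression, t(8) | 4.2–4.9% |

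A separate run with 40-point quadrature and 1,500 replicates per setting gave 13.5–15.3% for ML Wald z. At ICC 0.02 ML Wald z is still 11.5%. Without strata terms ML Wald z gives about 9–11%.

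**Step 4: power on 8 df.** At 50 per hospital, ICC 0.08 and r = 0.1, the design effect is 1 + 49×0.08 = 4.92. The variance is 0.4075 × 0.99 × 4.92/300 = 0.006616, so SE = 0.0813 and 0.25/SE = 3.07. Table 2's approximation gives Φ(3.07 − 2.23) = 80.1%. The exact noncentral t gives 79.1% on 10 df and 76.8% on 8 df. Put into the Table 2 formula, t(8) = 2.306 gives n = 64.60, × 0.99 = 63.95, m = 66.56, so 67, or 402 per arm.

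**The case against.** The strongest reply is that the article never commits to maximum likelihood, a Wald test or a z reference. Estimation method and degrees of freedom are ordinary content for an analysis plan that is not shown, and Table 2 suggests that the designers knew about the few-cluster problem. This stands in part. A reader might infer that the protocol specifies a test with a 14–15% false-positive rate; the text does not support that. The figure belongs to the worst common implementation.

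What the reply does not remove is that the article itself fixes the model, the stratum adjustment, the 12 hospitals and the 5% level. Every uncorrected version tested exceeds that level, and the design calculation used a different basis from any of them.

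Two further inferences also go too far. One is that no positive result could be trusted. By the scaling in Step 2, an ML Wald z above about 2.306 × √(12/8) = 2.82 (nominal p about 0.005) would also pass a 5% t(8) test, so the doubt falls on results between roughly 1.96 and 2.82. The other is that all secondary endpoints share the headline inflation. Stratum adjustment is stated only for the main outcome, so the 9–11% figure is the relevant one for binary secondary outcomes under ML Wald z. Linear mixed models for continuous secondary outcomes were not simulated separately.

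**Conclusion.** The point holds in conditional form. As described and without a small-cluster correction, the primary analysis does not keep the two-sided 5% level: about 8–9%, 11–13% or up to 14–15%, depending on implementation. It also does not match the t-based inference behind Table 2. Even the design's 10 degrees of freedom become 8 once the strata enter the model.

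The figures assume that catchment size enters as a three-level factor (a single linear term would leave 9 df), that there are no true stratum effects, and that no patient covariates are in the fitted model. The t basis of Table 2 is inferred from reproducing its cells; the article does not state it. The 77% power figure assumes that the strata leave the ICC at 0.08. If stratification removes between-hospital variance, the loss is smaller. Neither design nor data collection is affected, so this can be settled fully before the primary analysis.

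**What to change.** Keep the mixed logistic model for the odds ratio. State that the primary p-value and confidence interval come from inference valid for 12 clusters, by one of two routes:

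- REML-type estimation with a t reference on 8 df (Kenward–Roger or Satterthwaite type). Name the software routine and confirm its level by a short simulation, because the 5.0–5.7% above comes from a linear model.
- A two-stage analysis: patient-level covariate adjustment, then hospital-level residuals regressed on arm and strata with t on 8 df.

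A within-stratum permutation test can support either route. There are 6 × 6 × 6 = 216 possible allocations. Replacing z by t(8) while keeping the maximum-likelihood variance is not enough, since about 9% remains. For continuous secondary outcomes, use REML with small-sample degrees of freedom. For binary secondary outcomes, use the same approach as for the primary, with degrees of freedom matching the terms fitted.

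The cost is some analysis-plan text, a little code and wider intervals. Power at ICC 0.08 and r = 0.1 should be restated as about 77% on 8 df, against the planned 80%.

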### Study objectives and endpoints

The primary study objective is to investigate the effects of the complex intervention by comparing the use of chemotherapy in the last 3 months of life between the intervention and control groups. This will be assessed using the following primary endpoint: the proportion of patients who receive chemotherapy during their last 3 months of life; and, by the first secondary outcomes, the number of cycles administered in this period, time from initiation of last cycle to death, and average time from discontinuation of last cycle to death.

Additional secondary objectives focus on: (1) the use of medical interventions / treatments at the EoL; and (2) patient- and caregiver-reported outcomes. The first will be assessed by the proportion of patients who receive this, as with the primary outcome. Patient- and caregiver-reported outcomes will be assessed every other month using well-validated questionnaires. These endpoints are defined as average area under the curve of follow-up assessments for each outcome.

Exploratory analyses will also investigate potential differences in length of survival between the two arms and examine potential differences in direct costs of care (Table 1).

**Table 1 Tab1:** Primary, secondary, and explorative objectives, and related endpoints and assessments

	Objectives	Endpoint	Assessment method
Primary	To compare use of chemotherapy in the last 3 months of life in the control and intervention groups	Proportion of patients who receive chemotherapy at EoL	Numerical and descriptive data from HCP registrations/e-CRF, last 3 months before death
Secondary	To examine the administration of chemotherapy last 3 months, medical interventions/treatments at EoL, after discontinuation of chemotherapy	Number of chemotherapy cycles, initiation, and discontinuation Proportion of patients who receive other medical interventions, i.e. concomitant medication and artificial nutrition	Numerical and descriptive data from HCP registrations/e-CRF, last 3 months of life, and after discontinuation of chemotherapy
	To compare PROs	Patient-reported symptom burden, QoL, anxiety/depression, satisfaction with information	EAPC basic dataset. EORTC-QLQ PAL15, PHQ-9, GAD-7, EORTC QLQ-INFO25
	To compare caregiver-reported outcomes	Caregiver-reported health, QoL, and satisfaction with care	SF-36, FAMCARE

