**Table 4 Tab4:**
[figure not shown]
Study schedule, according to the Standard Protocol Items: Recommendations for Interventional Trials (SPIRIT) guidelines

^1^Self-reported data are collected up to seven times during the first year, or until the patient’s death or study withdrawal, whichever comes first. As final date for inclusion is 31 December 2020, patient follow-up will continue in 2021

^2^Caregivers receive two forms at 6 and 12 months after the patient is dead, provided that they consent to continue in the study. Thus, caregiver follow-up may continue in 2022

^3^Educational program for physicians to be completed before patient enrolment

^4^All study forms are similar in both arms

^5^Sociodemographic data that are unlikely to change over time are only registered at baseline

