### The EAPC basic dataset: background information and symptoms

This part of the patient form is similar to the EAPC basic dataset [68] with a few adaptations to the present study. The form contains 14 questions: sociodemographic variables, i.e. date of birth, date of consent, and marital, living, educational, and working status, followed by ethnicity, use of tobacco and alcohol, and five questions on height and weight, nutritional status, and intake modified from the SGA [71]. For subsequent forms, one question about use of healthcare services since inclusion has been added, whereas general background items that are unlikely to change between assessments have been dropped, to reduce respondent burden.

This form contains 12 frequent cancer-related symptoms: pain; drowsiness; tiredness; nausea; appetite; dyspnea; depression; anxiety; wellbeing; sleep; constipation; and vomiting. The period is right now, and patients are asked to rate the intensity on a NRS of 0–10 (0 = no pain/no dyspnea, etc. to 10 = worst imaginable pain/dyspnea, etc.).

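### As written, the models for overall QoL, QLQ-INFO25, SF-36 and FAMCARE omit the outcome's own baseline score, and no caregiver-level covariate is named for caregiver outcomes

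*Protocol article*

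**What the plan says.** The Statistics section describes mixed-effects logistic and linear models for the primary and secondary endpoints and states that "all models will be adjusted for potentially relevant baseline covariates at patient level, i.e. sex, age, diagnosis, performance status score, and baseline symptom scores". The abbreviation i.e. closes the list. The only addition is catchment-area size, and that is for the main outcome.

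For patient- and caregiver-reported outcomes, Study objectives and endpoints says: "These endpoints are defined as average area under the curve of follow-up assessments for each outcome". Table 1 gives the patient-reported endpoints as "Patient-reported symptom burden, QoL, anxiety/depression, satisfaction with information", so QoL, depression and information stand apart from symptom burden. It gives the caregiver endpoints as "Caregiver-reported health, QoL, and satisfaction with care", measured by SF-36 and FAMCARE.

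On timing, footnote 1 to Table 4 says: "Self-reported data are collected up to seven times during the first year". Forms are sent every other month, so this fits one form at baseline and six afterwards.

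**The concern.** For most of these outcomes the patient's or caregiver's own starting score is likely to be the strongest single predictor of later scores. Here it enters neither through the endpoint, which uses follow-up only, nor through the covariates, except for symptom outcomes.

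Two things are at stake. The first is precision: variance that a baseline score would explain stays in the residual. The second is protection against imbalance. There are six hospitals per arm, the trial is not blinded, and intervention hospitals complete their training before recruiting. Eligibility rests partly on judgement (anticipated last line of chemotherapy, expected survival under 12 months). Patients and caregivers therefore enter after their hospital's arm is known, and the arms may differ at baseline by chance or systematically.

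**Working it through.** **1. The plan's own figure.** The 300 per arm in Table 2 (ICC 0.08, r_adj 0.1) belongs to the primary binary endpoint. With six hospitals per arm, 20% versus 45%, two-sided 5% and 80% power:

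- Patients per arm without clustering = (t(0.975, 10 df) + z(0.80))² × (p1q1 + p2q2) × (1 − r²) / d² = (2.228 + 0.842)² × 0.4075 × 0.99 / 0.0625 ≈ 60.8.
- Patients per hospital = 60.8 × 0.92 / (6 − 60.8 × 0.08) ≈ 49.35, rounded up to 50, and 50 × 6 = 300.

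The figure reproduces. Chemotherapy use in the last 3 months of life has no baseline value, so nothing below changes it.

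**2. Which baseline enters which model.**

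| Outcome | Own baseline among the listed covariates? |
|---|---|
| Symptom burden | Yes |
| Depression (PHQ-9) | Arguably, as a symptom score |
| Overall QoL (QLQ-C15-PAL) | No, but partly proxied by symptoms |
| Information (QLQ-INFO25) | No |
| Caregiver health and QoL (SF-36) | No; no caregiver covariate named |
| Caregiver satisfaction (FAMCARE) | No; no caregiver covariate named |

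**3. How large a chance imbalance could be.** Assumed, because the documents do not give them: a baseline ICC of 0.02 to 0.05 and m = 30 to 50 analysed per hospital (50 is the planned mean; 30 allows for missing forms). The standard error of the between-arm baseline difference, in SD units, is sqrt((2/6) × (ICC + (1 − ICC)/m)).

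- ICC 0.02, m = 50: sqrt(0.333 × 0.0396) = 0.115. P(|difference| ≥ 0.2 SD) ≈ 8%.
- ICC 0.05, m = 30: sqrt(0.333 × 0.0817) = 0.165. P(|difference| ≥ 0.2 SD) ≈ 22%.

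**4. How much of a 0.2 SD imbalance reaches the estimate.** Let rho be the correlation of own baseline with the follow-up average (assumed 0.4 to 0.6), and s the correlation of the listed symptom scores with the own baseline (assumed 0.2 to 0.6). Suppose symptoms predict the outcome only through the own baseline. The carry-over is then 0.2 × rho × (1 − s²).

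- rho 0.4, s 0.6: 0.2 × 0.4 × 0.64 = 0.051 SD.
- rho 0.6, s 0.2: 0.2 × 0.6 × 0.96 = 0.115 SD.

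**5. Precision.** Assume the listed covariates already explain 10% of the variance, and that the model including the own baseline explains R² = 0.25 to 0.36 (rho 0.5 to 0.6).

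- If the baseline acts within hospitals only, the variance cut is 1 − [ICC + (1 − ICC)(1 − R²)/m] / [ICC + (1 − ICC) × 0.9/m]. With ICC 0.05, m = 45, R² 0.25: 1 − 0.0658/0.0690 = 4.6%. With ICC 0.02, m = 30, R² 0.36: 1 − 0.0409/0.0494 = 17.2%.
- If it also explains hospital differences, the cut is 1 − (1 − R²)/0.9. That is 1 − 0.75/0.9 = 16.7% to 1 − 0.64/0.9 = 28.9%.

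**The case against.** The strongest reply is that a condensed article may leave outcome-specific covariates to the analysis plan, and that the list is worded as potentially relevant covariates. Silence would indeed be no finding. But the article is not silent: it gives one closed list for all models, and that list does not fit these endpoints.

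Several stronger readings are tempting and are not supported:

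- **That the Sample size section promises baseline adjustment for these outcomes.** It says: "Effects on power increase due to adjustment by baseline measurements and other covariates (see statistical analysis section for the full list of covariates proposed". That sentence concerns power for the primary binary endpoint. It calls the list full but makes no commitment about patient- or caregiver-reported models.
- **That depression is left out.** The PHQ-9 section describes the instrument as measuring depressive symptoms, and the EAPC form is described thus: "This form contains 12 frequent cancer-related symptoms: pain; drowsiness; tiredness; nausea; appetite; dyspnea; depression; anxiety; wellbeing; sleep; constipation; and vomiting". Baseline symptom scores can reasonably be read to cover the PHQ-9, and the depression, anxiety and wellbeing items partly stand in for overall QoL.
- **That the plan prescribes adjusting caregiver outcomes for the patient's characteristics.** The level named in the list may simply mean individual as opposed to hospital. What can be said is that no caregiver covariate is named.
- **That baseline scores are certainly in hand.** Table 4 is not shown. Seven forms in a year fits a baseline form, but which instruments it carries cannot be confirmed.

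Two further objections stand. The 8% to 22% in step 3 is chance imbalance, which the standard error already reflects and which is not bias; systematic imbalance from recruitment after allocation is possible but not quantified. And the first mailed QLQ-INFO25 and FAMCARE forms may be completed after the intervention has begun, because physicians are trained before inclusion and collaboration with palliative care starts at inclusion. Conditioning on such a score could remove part of the effect. FAMCARE also measures satisfaction with palliative care, while people already in a palliative care programme are excluded.

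**Conclusion.** The point holds for secondary endpoints. Overall QoL, QLQ-INFO25, SF-36 and FAMCARE are, as written, analysed without their own baseline, and caregiver models have no caregiver covariate named. The gap is clearest for the caregiver outcomes and QLQ-INFO25, and partly proxied for QoL.

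A 0.2 SD imbalance would carry about 0.05 to 0.12 SD into the estimate at correlations of 0.4 to 0.6. A reader might take 0.10 to 0.12 SD (0.5 to 0.6 × 0.2) as the figure, but that ignores the covariates already listed. The avoidable part of the effect variance is about 5% to 29% at correlations of 0.5 to 0.6, depending on the ICC and on whether the baseline also explains hospital differences. All these correlations and ICCs are assumptions. This is worth correcting before analysis, but it does not threaten the trial's main conclusion.

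**What to change.** Add to the covariate rule in the Statistics section that each patient- and caregiver-reported model also includes the baseline score of the same instrument, where collected before exposure to the intervention. Add that caregiver models use the caregiver's own baseline score and the caregiver background data that the trial already records. For QLQ-INFO25 and FAMCARE, put the baseline score in the main model only if the first form precedes intervention contact; otherwise report that adjustment as a sensitivity analysis.

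The cost is a few lines of text and, if the first form carries these instruments, no new data collection. There are two downsides. Missing baseline scores need simple imputation so that no patient or caregiver is dropped. A baseline form completed after the intervention starts could absorb part of the effect, which is why the timing condition is needed.
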